**Figure 1 figure1:**
[figure not shown]
Participant flow.

### Participants

We will seek to recruit 38 adult (≥18 years) patients diagnosed with either primary or secondary glioblastoma who are scheduled to receive standard radiation (>65 years old, 3 weeks; <65 years old, 6 weeks) and concurrent and adjuvant temozolomide chemotherapy postsurgical debulking or biopsy. Patients will be recruited through the neurooncology clinic at the Nova Scotia Health Cancer Center. Participants will be screened by [name] and deemed eligible based on the following criteria: (1) histologically confirmed diagnosis of either primary or secondary glioblastoma, (2) received any dose of DEX, (3) Karnofsky Performance Status (KPS) >70, (4) English fluency, (5) physician approval, and (6) willingness to travel to Halifax to participate. Exclusion criteria include (1) unstable or symptomatic cardiac or pulmonary disease, injury, or comorbid disease that precludes ability to safely exercise; (2) significant cognitive limitations or lacking sufficient mental capacity to give consent (eg, mental health conditions such as schizophrenia, dementia, and brain injury); and (3) uncontrolled seizures associated with impaired awareness. Capacity to provide consent will be assessed through a verification of comprehension through several embedded questions in the informed consent. These questions will ascertain a patient’s ability to understand what is being asked of them as a potential research participant.

### Standard of Care

Standard treatment for glioblastoma after biopsy or surgical debulking involves a combination of daily oral temozolomide chemotherapy given with daily radiation (5 days/week) for 3 weeks to 6 weeks for a final radiation dose of 40-60 Gy given in 15-30 fractions, respectively. Generally, patients <65 years old receive 6 weeks of radiation with daily temozolomide. Due to poor tolerance of this high dose, patients >65 years old, or those with aggressively growing tumors, receive the same general regime but for 3 weeks. For those between the ages of 65 years and 70 years, 3 weeks or 6 weeks of radiation is chosen based on underlying fitness. Radiation can only be given at the cancer center, so patients attend appointments in person each day. It is during this time that patients may have their steroid dose increased to control the edema associated with radiation. Once radiation is completed, there is a 1-month recovery period, during which there is further adjustment of steroid dose, as needed. Stable patients will continue temozolomide on its own, where it is taken for 5 days a month for 6 months. Throughout this time, patients are examined monthly and monitored every 2 months with magnetic resonance imaging (MRI) of the brain to assess tumor response and guide requirements for further steroid adjustment.

All study patients will receive standard of care treatment. Participants allocated to the CON group will be advised to maintain an active lifestyle but will not receive any formal exercise prescription. CON participants will be given the opportunity to participate in the same intervention following the 12-week control period.

### Intervention and Study Setting

Following baseline assessments, participants allocated to the EX group will meet with a CEP at our hospital-based exercise lab. Here, participants will receive an individually tailored, circuit-based resistance training program. Circuit-based resistance training is a common training method used to foster aerobic fitness, muscular endurance, and strength, as well as neuromuscular adaptations in 1 workout. Circuit-based resistance training is comprised of several sets of different exercises with little rest in between each set [50]. EX participants will be asked to return to the lab for 3 to 4 supervised sessions per week for 12 weeks. Sessions will be designed to coincide with standard of care visits to reduce participant burden.

Participants will begin with a light-to-moderate-intensity (3-6 on the 10-point Borg Scale), systematically progressed, circuit-based resistance training program for 20 minutes to 30 minutes per session. Each session will consist of 3 circuits. Each circuit will involve 3 sets of 3 different exercises (20-second intervals for a total of 1 minute per set; short rest between exercises will be provided as needed). Each set will be followed by a 1-minute break. Figures 2 and 3 describe a sample training program and progression. Following the first 3 weeks to 6 weeks of supervised exercise sessions (coinciding with treatment protocol), participants allocated to the EX group will be asked to attend a minimum of 1 in-person session per week for the remaining 6 weeks to 9 weeks of the 12-week program. To reduce participant burden, participants will be offered the option of completing the remaining 2 to 3 weekly exercise sessions at home (supported virtually as needed or preferred). For those living in the Western zone, following the first 3 weeks to 6 weeks of the program, delivered at our hospital-based exercise lab, in-person programming will also be offered at our partner site in Wolfville, Nova Scotia (Acadia University) under the supervision of a CEP. Participants will have the option of completing more than one or all weekly exercise sessions in person at either site. Initial exercise prescriptions will be developed and modified as needed by a CEP in accordance with the participant’s health and fitness status. Physician referral, individually tailored, and short, lighter intensity resistance training sessions have been designed to foster program adoption and adherence [51].

**Figure 2 figure2:**
[figure not shown]
Introductory resistance-based exercise circuit (whole body).

**Figure 3 figure3:**
[figure not shown]
Intermediate and advanced resistance-based exercise circuit.

### Measures

#### Sociodemographic Characteristics

Sociodemographic characteristics will include age, sex, gender, level of education, ethnicity, annual household income, and employment status.

#### Medical History and Performance Status

Medical information will include surgical date and procedure (biopsy/resection), tumor characteristics, treatments received, neurological deficits, treatment-related side effects using the International Common Toxicity Criteria Adverse Event (CTCAE) [52], comorbidities, and prescription medications. Performance status will be evaluated using the KPS [53], assessed by [name] at the time of study enrollment and following the completion of the study.

The primary outcome measure is steroid-induced myopathy as determined by functional performance. Functional performance will be assessed using the Short Physical Performance Battery (SPPB) test [54,55] and handgrip strength [14]. The SPPB uses tasks that mimic activities of daily living and examines 3 areas of lower body function: gait speed, balance, and muscular endurance. Grip strength will be evaluated using a handheld dynamometer. Mean handgrip strength will be calculated from a total of 4 measurements (2 with the right hand and 2 with the left hand) and recorded to the nearest 0.1 kg [56].

Secondary outcome measures will include body composition, aerobic fitness, vital measurements (ie, resting blood pressure and heart rate), physical activity, general health, QOL, fatigue, and cognitive functioning. Participant accrual, attrition, program adherence, reasons for missed sessions, and adverse events will be documented. Body composition measures will include body mass index (kg/m^2^), arm circumference, waist circumference, calf circumference [57,58], and muscle mass and quality. Muscle density and intramuscular adipose tissue will be assessed using whole-body MRI [59]. Flex processing will be used to construct muscle, fat, and water images. All scans and imaging processing will be performed using a 3T MRI and associated software at Biotic Imaging for Life. Aerobic fitness will be measured using the 6-minute walk test (6MWT) [60]. The 6MWT is an effective measure of physical functioning in recurrent primary malignant gliomas [61]. General health will be assessed using the EQ-5D-5L [62,63]. The EQ-5D-5L is a valid, widely used tool that measures patient health across 5 dimensions (mobility, self-care, usual activities, pain/discomfort, and anxiety/depression) [62,63]. QOL will be assessed using the 50-item Functional Assessment of Cancer Therapy-Brain (FACT-Br), which provides scores for physical, functional, emotional, and social and family well-being as well as a brain cancer–specific subscale [64]. Fatigue will be measured using the 13-item Functional Assessment of Chronic Illness Therapy-Fatigue (FACIT-F) [65]. Both the FACT-Br and FACIT-F have been extensively validated and are reliable and widely used tools in the oncology setting [65-67]. Self-reported exercise will be assessed using the Godin Leisure-Time Exercise Questionnaire (GLTEQ) [68-70]. The GLTEQ is a well-validated questionnaire that assesses the frequency and duration of mild, moderate, and vigorous leisure-time exercise participation [70]. Objective physical activity will be captured through a wristworn Garmin activity tracker. Cognitive functioning will be assessed using the Trail Making Test [71] for executive function and the Hopkins Verbal Learning Test-revised for memory [72-74].

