**Methods:**

This is a 2-armed, randomized controlled trial with repeated measures. We will recruit 38 adult (≥18 years) patients diagnosed with either primary or secondary glioblastoma who are scheduled to receive standard radiation and concurrent and adjuvant temozolomide chemotherapy postsurgical debulking and received any dose of DEX through the neurooncology clinic and the Nova Scotia Health Cancer Center. Patients will be randomly allocated to a standard of care waitlist control group or standard of care + circuit-based resistance training exercise group. The exercise group will receive a 12-week individualized, group and home-based exercise program. The control group will be advised to maintain an active lifestyle. The primary outcome, muscle myopathy (functional fitness), will be assessed using the Short Physical Performance Battery and hand grip strength. Secondary outcome measures will include body composition, cardiorespiratory fitness, physical activity, QOL, fatigue, and cognitive function. All measures will be assessed pre- and postintervention. Participant accrual, exercise adherence, and safety will be assessed throughout the study.

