### Sample Size

Sample size is based on a meaningful change (effect size 0.30) in physical performance [75]. A sample of 24 (12 per group) will allow us to detect differences as small as 0.3 points to 0.8 points on the SPPB with 80% power based on an ɑ=.05 with no sphericity correction. Although randomization should account for variations in sex, we will strive to enroll 38 participants (see the Feasibility section) to explore this covariate.

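### SPPB and handgrip strength share the primary outcome with no ranking or success rule, while the sample size rests on SPPB alone

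*Protocol article*

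**What the plan says.** The Measures section of the protocol article (Medical History and Performance Status) defines one primary construct: "The primary outcome measure is steroid-induced myopathy as determined by functional performance". It then names two instruments for it: "Functional performance will be assessed using the Short Physical Performance Battery (SPPB) test [54,55] and handgrip strength [14". The Abstract (Methods) pairs them in the same way: "The primary outcome, muscle myopathy (functional fitness), will be assessed using the Short Physical Performance Battery and hand grip strength".

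The instruments do not feed one score. SPPB covers the lower body through gait speed, balance and muscular endurance. Grip is a dynamometer reading in kg: "Mean handgrip strength will be calculated from a total of 4 measurements (2 with the right hand and 2 with the left hand". The article gives no composite and no order, and does not say whether one measure or both must favour exercise.

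The Sample Size section reads: "Sample size is based on a meaningful change (effect size 0.30) in physical performance [75". It continues: "A sample of 24 (12 per group) will allow us to detect differences as small as 0.3 points to 0.8 points on the SPPB". The stated power is 80%, at an alpha of .05. It gives no effect or detectable difference for grip. It justifies the larger target of 38 by the wish to explore sex. The Statistical Analyses section applies one mixed model (group and time as fixed factors) to the study outcomes and states no significance level or success rule.

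**The concern.** The outcome section gives SPPB and grip equal standing, while the sizing section treats SPPB as the only measure that matters. One construct assessed on two scales still yields two estimates and two p-values, and these can disagree. A programme might improve leg function and leave grip unchanged, or the reverse, and the article does not say which result would decide.

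An open rule can be closed after the results are known. The trial could then be reported as positive on whichever measure moved, or on a both-or-either rule chosen to suit. The stated alpha and power describe one test of one measure. Whether they describe the eventual primary claim depends on a rule that is not written down.

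**Working it through.** **Inputs from the article.** Effect size 0.30 (metric not stated), N = 24 (12 per group), alpha .05, power 80%, two groups, two time points, target 38.

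**Assumptions not in the article.** The 0.30 is Cohen's f for the group-by-time effect. The pre-post correlation of a measure is ρ = 0.5. The correlation r between the two test statistics is varied. Where grip power is needed, grip has the same f as SPPB.

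**Step 1. Reproduce the stated sample size.** For a repeated-measures group-by-time F test with m = 2 times, λ = f² × N × m / (1 − ρ), with 1 and N − 2 degrees of freedom.

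λ = 0.09 × 24 × 2 / 0.5 = 8.64 on 1 and 22 df. At alpha .05 the power is 80.2%, and 24 is the smallest even N that reaches 80%. The stated figure is therefore reproduced for one endpoint at an undivided .05. Other readings of 0.30 do not give 24: a between-group effect with f = 0.30 needs 68, and two means at d = 0.30 need 350 (two-sided).

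**Step 2. Rule A: either measure at .05 is enough.** If the tests are independent, the family-wise error is 1 − 0.95² = 9.75%. For correlated tests it is 1 − P(|Z₁| < 1.96 and |Z₂| < 1.96) under a bivariate normal:

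| r between tests | Family-wise error |
|---|---|
| 0 | 9.75% |
| 0.3 | 9.5% |
| 0.5 | 9.1% |
| 0.7 | 8.3% |
| 0.9 | 7.0% |

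**Step 3. Rule B: both measures must succeed at .05.** There is no inflation. With 80% power for each, joint power is 0.80 × 0.80 = 64% if independent. From the bivariate normal it is 67% at r = 0.3, 69% at r = 0.5 and 71% at r = 0.7. To reach 80% jointly with independent tests, each needs √0.80 = 89.4% power, which takes N = 32 under the Step 1 model.

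**Step 4. Rule C: alpha split to .025 each.** At N = 24, λ is still 8.64 and power per measure falls from 80.2% to 70.1%. At N = 38, λ = 0.09 × 38 × 2 / 0.5 = 13.68 on 1 and 36 df, and power is 90.8%. These figures are sensitive to ρ:

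| ρ (pre-post) | N for 80% at .05 | N for 80% at .025 | Power at .025, N = 24 | Power at .025, N = 38 |
|---|---|---|---|---|
| 0 | 46 | 56 | 39% | 61% |
| 0.3 | 34 | 40 | 54% | 78% |
| 0.5 | 24 | 30 | 70% | 91% |
| 0.7 | 16 | 20 | 91% | 99% |

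Only ρ = 0.5 is consistent with the article's own 24 under this model.

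**Step 5. Rule D: SPPB alone is primary.** Alpha stays at .05, N at 24 and power at 80.2%. Of the four rules, this is the one that the Sample Size section already matches.

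**The case against.** **The analysis plan may settle it.** This is a condensed article, and the mechanics of multiplicity (order of testing, alpha split) are commonly left to an analysis plan. That stands for the mechanics, and their absence is not the finding. Which variable is primary is a matter for the protocol, and here the protocol names two and powers one.

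**It is one outcome, and the wording may mean both.** The two instruments are joined by a plain conjunction under a single construct. This allows a both-must-succeed reading, under which no error rate is inflated. The objection stands, and it limits the claim. A reader might infer that the trial gives itself two chances at .05 and so has nearly double its stated false-positive rate. The article does not support that. It never says that either result suffices, and it never says that each measure is tested at .05. Its only .05 is an input to the SPPB power statement.

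**Thirty-eight participants would absorb it.** On the Step 1 assumptions, 38 analysable participants give 90.8% power per measure at .025. Power at .05 is 94.9% each, so a both-must-succeed rule would have about 0.949² = 90% if the tests are independent. It would therefore be wrong to call an alpha split unaffordable. However, 38 is an aspiration justified by exploring sex, no allowance for dropout is stated, and the effect on grip is assumed.

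**The remedy is a choice.** Several rules are valid. Nothing in the article requires handgrip to be tested only after SPPB.

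**Conclusion.** The point holds in a limited form. The protocol article names two separately scored measures as its primary outcome without ranking or combining them, and sizes the trial on one of them. The fault is an open success rule.

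The consequence depends on how the rule is closed. Under an either-suffices rule, family-wise error is about 7% to 10%. Under a both-must-succeed rule there is no inflation, and joint power at 80% each is about 64% (independent) to 71% (r = 0.7). With alpha split, power per measure is about 70% at N = 24 and about 91% with all 38 analysable. At N = 24, each of these departs from the stated alpha or the stated power.

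That two unranked measures are named and only SPPB is powered rests on the text alone. The error rates assume correlations between tests that the article does not give. The alpha-split figures assume f = 0.30 for the group-by-time effect, ρ = 0.5 and an equal effect on grip. A near-doubling of the error rate is one conditional outcome and should not be reported as a property of the plan.

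**What to change.** Name the week-12 SPPB total score, compared between arms, as the single primary outcome at two-sided .05. This agrees with the measure and alpha in the Sample Size section, which does not state sidedness. Make mean handgrip strength a key secondary outcome and report it with a 95% CI whatever the SPPB result. Testing it in fixed sequence after SPPB is one acceptable option: it takes no power from SPPB and is not essential. Align the Abstract and the Measures section, and make the change before outcome data by arm are seen.

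If the investigators want to keep both measures as primary, they should state the rule (either with an alpha split, or both required), give an assumed effect for grip, and recompute the sample size.

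The recommended change costs wording only, and N = 24, alpha .05 and the model are unchanged. The downside is that handgrip can no longer carry the primary claim on its own.

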### Sample Size

Sample size is based on a meaningful change (effect size 0.30) in physical performance [75]. A sample of 24 (12 per group) will allow us to detect differences as small as 0.3 points to 0.8 points on the SPPB with 80% power based on an ɑ=.05 with no sphericity correction. Although randomization should account for variations in sex, we will strive to enroll 38 participants (see the Feasibility section) to explore this covariate.

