### Study Design and Procedures

This manuscript has been written in accordance with the Standard Protocol Items for Randomized Trials (SPIRIT) 2013 guidelines [49]. This is a 2-armed, randomized controlled trial with repeated measures. Eligible participants will be referred to our exercise lab located at the Nova Scotia Cancer Center, Halifax, Nova Scotia, Canada. Here, they will provide informed consent, complete a baseline survey, and undergo a comprehensive functional fitness assessment conducted by a clinical exercise physiologist (CEP). Following baseline assessments, participants will be randomized 1:1 to either the 12-week exercise intervention (EX) or standard of care, waitlist control group (CON). Block randomization in groups of 4 will be used to ensure an equal balance of participants in each group throughout the study period. The allocation sequence will be concealed from the project coordinator who will be involved in assigning patients to groups. Given the nature of the exercise-based intervention, it not possible to blind participants or the CEPs to group allocation. All participants will return to the exercise lab at the end of the 12-week study to complete a final assessment (Figure 1).

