### Statistical Analyses

Descriptive statistics will be used to describe the population, accrual, program adherence, and safety. Study outcome measures will be assessed pre- and postintervention and will be analyzed using an intention-to-treat approach. A multiple imputation model will be used to account for any missing data. All participants will then be entered into a mixed effects model with participant group assignment at randomization and time point (pre- and posttest) as fixed factors and participant entered as a random factor. Due to feasibility in recruiting participants in the allotted time, the study will not be fully powered to detect sex-based differences; however, effect sizes associated with the intervention will be calculated and presented for each sex.

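### The claim that 12 patients per group can detect 0.3 to 0.8 SPPB points with 80% power does not follow from the stated inputs, unless the SD of change is as small as about 0.25 to 0.67 points

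*Protocol article*

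**What the plan says.** The Sample Size section opens with "Sample size is based on a meaningful change (effect size 0.30) in physical performance". It then makes the claim at issue: "A sample of 24 (12 per group) will allow us to detect differences as small as 0.3 points to 0.8 points on the SPPB". The power given is 80%, and the calculation is described as "based on an ɑ=.05 with no sphericity correction". The larger recruitment target has a different purpose, which is to look at sex: "we will strive to enroll 38 participants (see the Feasibility section) to explore this covariate".

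Under Measures, the SPPB is named, with handgrip strength, as the assessment of the primary outcome. Study Design and Procedures gives 1:1 allocation. Statistical Analyses describes a mixed model with group and "time point (pre- and posttest) as fixed factors and participant entered as a random factor".

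The article does not say whether 0.30 is Cohen's f or a standardised mean difference. It gives no SD for the SPPB, no pre-post correlation and no step from the effect size to points.

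**The concern.** An effect size of 0.30 stands next to a difference of 0.3 to 0.8 points, so a reader will take the trial as sensitive to a small benefit. With 12 patients per arm, a two-arm comparison normally has 80% power only for a difference well above one SD. The two statements agree only if SPPB change hardly varies between patients.

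This affects how the result is read. If 24 patients are said to be enough for a meaningful change as small as 0.3 points, a non-significant result can be taken as evidence that exercise gives no such benefit. If the real threshold is larger, that inference fails.

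**Working it through.** **Inputs from the article.** Effect size 0.30; N = 24, 12 per group; power 80%; alpha .05; two measurements; no sphericity correction (Sample Size and Statistical Analyses). **Assumed here:** pre-post correlation ρ, SD of change, two-sided testing.

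**1. Reproduce N = 24.** Take 0.30 as Cohen's f for the group-by-time interaction, with 2 groups, m = 2 and ρ = 0.5.

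- λ = f² × N × m / (1 − ρ) = 0.09 × 24 × 2 / 0.5 = 8.64, on 1 and 22 df.
- Power from the noncentral F is 0.802. With N = 22 it is 0.763, so 24 is the smallest balanced total that reaches 80%.
- The N depends on ρ: the same f needs 34 at ρ = 0.3 and 16 at ρ = 0.7.
- Other readings of 0.30 miss 24. A between-subject main effect with f = 0.30 needs 68 (ρ = 0.5). A standardised difference of 0.30 needs about 175 per arm (two-sample, normal approximation) or 88 in total (paired).

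**2. Express it as a difference between arms.** For a two-sample t test on change scores, the squared noncentrality is d² × n/2 = 6d² with n = 12. Setting 6d² = 8.64 gives d = 1.20. The same value follows from f directly: in the 2×2 interaction the arms' changes differ by 4 × 0.30 = 1.2 raw SD, and at ρ = 0.5 the raw SD equals the SD of change, because √(2(1 − ρ)) = 1. The exact 80% threshold from the noncentral t is 1.197 SD of change at 12 per arm and 0.934 at 19 per arm.

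**3. SD of change that the stated range needs.** 0.3 / 1.197 = 0.25 points; 0.8 / 1.197 = 0.67 points.

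**4. Detectable difference and power for assumed SDs of change** (two-sided alpha .05):

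| SD of change (points) | Detectable, 12/arm | Detectable, 19/arm | Power for 0.3, 12/arm | Power for 0.8, 12/arm |
|---|---|---|---|---|
| 0.25 | 0.3 | 0.2 | 80% | >99% |
| 0.67 | 0.8 | 0.6 | 18% | 80% |
| 1.0 | 1.2 | 0.9 | 11% | 47% |
| 1.5 | 1.8 | 1.4 | 8% | 24% |
| 2.0 | 2.4 | 1.9 | 6% | 16% |

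**5. The other reading.** Suppose 0.30 is a mean difference in raw SDs. In SDs of change it is 0.30 / √(2(1 − ρ)).

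- ρ = 0.5: 0.30, power 10.8% at 12 per arm and 14.7% at 19.
- ρ = 0.9: 0.30 / 0.447 = 0.67, power 35% at 12 per arm.
- 80% at 12 per arm requires √(2(1 − ρ)) = 0.30 / 1.197 = 0.251, so ρ ≈ 0.97.

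**The case against.** The strongest reply is that a threshold in SDs and a threshold in points conflict only once an SD is fixed, and the article fixes none. With an SD of change of 0.25 to 0.67 points the sentence is true. In raw units a high correlation helps: at ρ = 0.9 the threshold is 0.54 raw SD, so a raw SD of about 0.56 to 1.49 points would support the range. This stands. A reader might infer that 12 per group cannot detect 0.3 to 0.8 points, or that the calculation is an arithmetic error. The article supports neither, and its N of 24 reproduces.

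A reader might also infer that 0.3 and 0.8 contradict each other, since one N at one power has one threshold. That holds only for a single SD. An SD that varies 2.7-fold (0.8 / 0.3) would produce such a range.

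The contrast is inferred too. The within-subject time effect with f = 0.30 gives the same N of 24, so the calculation need not have been for the interaction.

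Finally, an article condenses a fuller protocol, and the absence of an SD or a correlation is not in itself a fault. That is fair. But the article does more than omit inputs: it prints a specific sensitivity for a primary outcome measure that its printed effect size and N do not yield without an undisclosed and small SD.

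**Conclusion.** The point holds as an unsupported claim, not as a proven impossibility. On the reading that reproduces N = 24, the design has 80% power for a between-arm difference of about 1.2 SD of change, and the stated points follow only if that SD is 0.25 to 0.67. On the standardised-difference reading, power at 12 per arm is about 11% at ρ = 0.5 and 35% at ρ = 0.9. Recruiting 38 does not settle it, because the threshold is still 0.93 SD of change.

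The article's own background makes so small an SD hard to take for granted. It reports steroid myopathy in about 10% of patients after two weeks of high-dose therapy and in up to 50% to 60% with long-term use. As an illustration only: if 10% of an arm lost one point and nobody else changed, the SD of change would be √(0.1 × 0.9) = 0.30, already above 0.25. If 15% lost two points, it would be 2 × √(0.15 × 0.85) = 0.71, above 0.67.

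The 1.20 and 0.93 figures rest on two-sided alpha .05 and complete data. In SDs of change they need no correlation. The match to f = 0.30 needs ρ = 0.5, which is assumed here. The SDs in the table are also assumptions.

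**What to change.** Revise the Sample Size section as follows:

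- Name the effect-size metric (apparently Cohen's f) and the contrast it refers to, with the pre-post correlation actually used.
- State that 12 per arm gives 80% power (two-sided alpha .05) for a between-arm difference of 1.20 SD of change, and 19 per arm for 0.93 SD of change.
- Convert these to SPPB points with a stated SD of change, or a range of SDs.
- Withdraw the 0.3 to 0.8 point claim unless a cited SD supports it.
- Commit to reporting the between-arm effect with a 95% confidence interval, and say that a non-significant result does not by itself exclude a benefit of that size.

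The change is to wording only and needs no extra patients. Its cost is that the stated sensitivity becomes less favourable.
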